### Participants

Study subjects will be recruited from the university’s students and staff through informational mailing lists at the University of Tartu in Estonia. They must be native speakers of Estonian, and between 18 and 50 years old. The upper age limit is applied because the WM capacities are known to decay in ageing speakers (see in [65]) and due to the COVID-19 pandemic, in which the older participants belong to the higher risk group. Speakers eligible for the study should have normal or corrected to normal vision (soft contact lenses included, glasses excluded), no diagnosed language impairments and normal hearing ability. Subjects will be reimbursed 5 euros for their participation in the study.

Since the experiment is designed such that samples of subjects are going to respond to samples of target trials, PANGEA web application (Power Analysis for General ANOVA designs; [79] provided an *a priori* power analysis. The PANGEA analysis (variation parameters set to PANGEA defaults) indicates that, given the small to medium effect size (d = 0.45), the recommended sample size of 60 subjects is suitable for achieving the statistical power (1-*β*) of 0.8 in the evaluation of the three main effects and the three-way interaction between the fixed effects. Due to the spontaneous nature of the task, not all of the subjects will perform expectedly on all target trials. Therefore, the number of subjects is increased by approximately 33% of observations. Therefore, the resulting sample size is 84 subjects. The estimated sample size is at the limit of the feasibility of planned phonetic analyses and the project’s timeline.

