#### Statistical analysis

The goal of the statistical analyses is to determine whether the scaling of sentence-initial pitch peaks in long sentences is affected by an independent effect of incrementality or by the simultaneous effects of incrementality and high mental load. As the manipulations of the factors Double Actor (agent vs patient) and Identity (same vs different) elicit short and long sentences (see in Materials), the combinations of these are reduced into a factor Sentence Length (short vs long) for the main analysis. Thus, the main analysis examines the effect of the interaction between Cognitive Load (low vs high) and Sentence Length (short vs long) on (i) the proportional duration of naming gazes at the first-mentioned actors, (ii) duration of naming gazes, (iii) the sentence-final pitch valleys, (iv) and the sentence-initial pitch peaks.

The four dependent variables (duration of naming gazes, proportional gaze durations, sentence-final F0 minima, sentence-initial F0 maxima) are modelled with separate linear mixed-effects regression analyses (LMER, as implemented in the *lme4* package in [82, 85]). All models include the interaction between Cognitive Load (low vs high) and Sentence Length (short vs long) as the fixed effect, the block and trial number as the covariate effects, and random intercepts and slopes for items and subjects. The analysis will be carried out using sum-to-zero coding of the fixed effects. To avoid the convergence issues, the models will be optimized following the procedures suggested in Bates et al. [82]. First, the continuous variables block and trial are centred and/or scaled for the statistical analyses. Second, the convergence tolerances are adjusted by applying an optimizing algorithm diverging from the standard test but which results in the converging model. Third, and only in case the previous measures do not yield the convergence of the model fit, the random effects structure will be simplified by removing the correlations term from the random effects structure. Finally, the significances of the model estimates are obtained with the help of the *lmerTest* package [86] in R [85]. The significances of the main effects and the interaction are determined at the threshold of p<0.05.

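### The 84 subjects do not follow from 60 plus about 33%, and the 0.8 power is not stated for the Cognitive Load × Sentence Length interaction that the main analysis tests

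*Protocol article*

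**What the plan says.** All the sample-size figures stand in the Participants section of the protocol article. The power tool was run with "variation parameters set to PANGEA defaults" and, "given the small to medium effect size (d = 0.45"), it found that "the recommended sample size of 60 subjects is suitable for achieving the statistical power" "of 0.8 in the evaluation of the three main effects and the three-way interaction between the fixed effects". Because not every subject will respond usably on every target trial, "the number of subjects is increased by approximately 33% of observations", and "the resulting sample size is 84 subjects".

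Under Statistical analysis, Double Actor and Identity are reduced to one factor, Sentence Length, and "the main analysis examines the effect of the interaction between Cognitive Load (low vs high) and Sentence Length (short vs long") on four outcomes. For sentence-initial pitch peaks, a significant two-way interaction is named as the result that would show that the length effect depends on load. Later in that section the three-way interaction of Double Actor, Identity and Load is listed among the exploratory analyses, and Identity is equated with Sentence Length. No power is given for any two-way interaction.

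**The concern.** There are two separate faults. First, the base, the percentage and the final number cannot all be right, and a reader cannot tell which is wrong or whether 33% is an added fraction or an expected loss. The allowance carries weight in this design. Under Pre-processing and data harvesting, only fluent transitive sentences are kept, fixation and latency cut-offs apply, and a subject stays in with as little as 25% of trials usable.

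Second, the quoted power belongs to the main effects and to an interaction that is only exploratory. A reader judging the main result, above all a non-significant interaction, would naturally set it against a 0.8 that was never stated for that test.

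**Working it through.** **Inputs.** Participants: base 60, increase about 33%, final 84, d = 0.45, power 0.8. Design: 64 target measurements per subject. Procedure: 16 lists, each seen five or six times.

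**Can 84 be reproduced?**
- 33% as an increase: 60 × 1.33 = 79.8, so 80.
- 33% as a loss to be replaced: 60 / (1 − 0.33) = 89.6, so 90.
- Inflating observations instead of subjects: 60 × 64 = 3840; 3840 × 1.33 / 64 = 79.8, again 80.
- Working back from 84: 84 / 60 = 1.40, a 40% increase; 1 − 60/84 = 0.286, a 28.6% loss. With 33% as the increase, the base would be 84 / 1.33 = 63.2, not 60.

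None of the forward calculations gives 84.

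**Do the lists explain it?** 84 / 16 = 5.25, 80 / 16 = 5 and 90 / 16 = 5.625. All three fit five or six viewings per list, so the list structure does not single out 84.

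**Size of the discrepancy.** If a third of trials were in fact lost, 84 × 64 × 0.67 = 3602 observations would remain against 3840 from 60 complete subjects, or 94%. If 33% is only an added fraction, 84 is 4 more than the 80 it implies.

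**Which effects have a stated power?**

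| Effect | Power stated in Participants | Role in Statistical analysis |
|---|---|---|
| Three main effects | 0.8 | Tested; a main effect of load is the expected result for proportional gaze duration |
| Load × Sentence Length | none | Main test; decisive for pitch peaks |
| Load × Identity × Double Actor | 0.8 | Exploratory |

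**Can the missing power be computed?** No. The default variance values, and the alpha and sidedness used in the power run, are not given, so even the base of 60 cannot be reproduced. A range check needs assumed variance shares: item 0.1 to 0.4, by-subject slope 0.02 to 0.10, residual 0.3. With 64 items nested in 8 cells, subjects crossed with items, a two-sided 0.05 test and d = 0.45 placed on the two-way contrast itself, power at 60 subjects runs from 0.70 to above 0.99. These shares are not figures from the article. The check shows only that the power could lie on either side of 0.8.

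**The case against.** Three counter-arguments deserve an answer.

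- **The percentage is only approximate, and 84 exceeds the literal 80.** It is true that there is no shortfall if 33% means an added fraction. But an approximate 33% does not stretch to 40%, and if 33% is an expected loss, 84 falls short of 90. The ambiguity is itself the fault.
- **The two-way contrast belongs to the same 2×2×2 design that was powered**, since Identity stands for Sentence Length. This is fair. If d = 0.45 applies to that contrast with similar variance components, its power may be close to the stated one. What remains is that the article does not say so, and quotes power for an exploratory term in its place.
- **No section plans to read a non-significant interaction as evidence against the account.** This also stands. The risk lies with the reader, not in a stated decision rule.

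A reader might go further and infer that the main test has far less than 0.8 power, because an effect confined to one cell is halved in the interaction contrast. The documents do not support this. Take the second scenario under Hypotheses, with only long sentences under low load raised, by D, so that the cells are 0, D, 0, 0. The Length main effect is (D + 0)/2 − 0 = D/2. The Load main effect is also D/2. The interaction contrast on the same scale, half the difference of differences, is D/2 too. A main effect of 0.45 then implies an interaction contrast of 0.45. The halving appears only if 0.45 is re-read as the length effect within low load alone, and the article attaches it to main effects and an interaction.

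**Conclusion.** Both faults hold as faults of statement. The final number does not follow from its inputs: 84 is 60 plus 40%, against 80 or 90 under the two usual readings of 33%. Power is stated for the main effects and an exploratory three-way term, and not for the two-way interaction that decides the pitch-peak hypothesis. The first conclusion rests on arithmetic alone, and the second on setting Participants beside Statistical analysis.

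It is not shown that power for the main test is below 0.8, or that 84 subjects are too few. Either would require the contrast to which d = 0.45 refers, the variance inputs and the expected loss, and the article fixes none of these.

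**What to change.** No further enrolment is needed, which matters because Participants already places the sample at the limit of feasibility.

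1. Keep 84 and restate the allowance as 60 plus 40%, tolerating about 28.6% loss of observations. If the base or the final number is the actual error, correct that instead. Say whether the percentage is an increase or an expected loss.
2. Re-run the power tool for the Cognitive Load × Sentence Length contrast (Load × Identity in the full design). State which contrast d = 0.45 describes, and report this power in place of the three-way figure.

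The analysis model need not change. The cost is a correction to one paragraph and one re-run. The drawback is that the stated allowance falls to 28.6% if 33% was meant as a loss, and the power reported for the main test may turn out lower than 0.8.

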### Procedure

Subjects will be recruited through university mailing lists. The study call will include a registration form that requests subjects to share information about their age, linguistic background, vision and language impairments, if known. Invitations are sent to subjects who conform to the study criteria (see above). Otherwise, the subjects will be thanked for their interest. Together with an invitation letter, subjects will also receive a letter reminding them about their responsibility not to spread any infections, especially COVID-19, and to respect the hygiene rules in the testing rooms.

Upon arriving at the recording room at the University of Tartu, subjects are asked to fill out and sign a consent form informing them about the risks of the study and their right to stop participating in the experiment at any time without any consequences. They will be introduced to the eye tracking method that is carried out with synchronous speech recording.

After these introductory parts, the subjects are asked to seat themselves in front of the desktop-mounted EyeLink 1000 Plus eye tracker and lean their forehead on the head support. The chin is left unsupported because the study requires subjects to speak.

Subjects will be semi-randomly assigned to the 16 lists of experimental trials such that each list will be seen five or six times. The order of the items within a block (low vs high load) is randomized. The items are subdivided into the blocks such that there is the least possibility for semantic overlap between the target and distractor items.

Once the calibration procedures are completed successfully, subjects receive a thorough explanation of their task by seeing a sample of five pictures together with a possible written description in the bottom part of the screen. They will be given an opportunity to ask as many clarification questions as needed.

The subjects’ task is to describe simple actions by mentioning all three depicted actors using either plural or coordinated NPs. Every picture is presented for 6500 ms (Fig 3). The speech recording starts at the exact moment that the picture is shown. When the task is clear, subjects will have 6 practice trials to rehearse, after which they can again ask questions. If necessary, subjects are calibrated once more before proceeding to the experiment.

**Fig 3 pone.0259343.g003:**
[figure not shown]
Presentation sequence of stimuli in trials without the concurrent memorization task.

Pictures are presented contingently to gaze. This means that a picture is only shown once the eyes move to the dot in the upper part of the screen. The gaze-contingent presentation ensures that subjects will always look at the dot in the upper part of the screen before seeing the picture. This procedure guarantees that all speakers begin processing of visual information at approximately the same time in all trials. Apart from the drift check, the experiment can proceed without any assistance or control from the experimenter and be interrupted at any point either for a break or quitting.

A break is enforced half-way through the trials to stimulate concentration on the task and to introduce the second block with the trials that are accompanied with the memorization task. First, subjects are presented with 6 practice trials with a task to memorize three words in their exact order and then after 2500 ms, to orally recall the memorized words and then indicate whether all of the memorized words are conventional with the verb on the screen or not. In particular, their task is to say if all of the words fit with the verb on the screen or not by either saying ‘Kõik sobivad’ (They all fit) or ‘Ei sobi’ (Not all words do fit). In the target trials, a correct response to a transitive verb prompt is that all words fit with the verb on the screen. For example, a ‘tradition’ or ‘search’ from the example in the Materials section (traditsioon, ‘tradition’, otsing, ‘search’, investor, ‘investor’) can be ‘continued’ and an ‘investor’ can ‘continue (with)’ something. The correct response to the intransitive verbs is that not all of the words fit. Consider the verb ‘worry’ paired with the nouns ‘tradition’, ‘search’ and ‘investor’ as an example. A ‘tradition’ or ‘search’ cannot ‘worry’ but an ‘investor’ can. Indeed, it is possible to worry about a tradition or search. However, within this particular task setting, this did not occur to our sample of the norming study because the accuracy scores for this word list was 1.0 when presented with the transitive verb ‘continue’ and 0.83 when presented with the intransitive verb ‘worry’. The target items are combined with pairs of nouns and a verb with the highest accuracy scores (see S1 Table).

The 6 memory trials are followed with 6 additional practice trials, in which memorization and recall are interposed by a task of picture description. Thereafter, the target and distractor pictures are always preceded by the list of three nouns in the middle of the screen for 2500 ms (Fig 4). Subjects are asked to remember the words in their exact order for later recall. After orally describing a picture, they are prompted with either a transitive or intransitive verb and are asked to recall the memorized words orally and to indicate whether all of the memorized words are conventional with the verb on the screen.

**Fig 4 pone.0259343.g004:**
[figure not shown]
Presentation sequence of stimuli in trials with the concurrent memorization task.

After completing the experiment, subjects are debriefed about the goals of the study, related research and a short list of literature. Together with the debriefing letter, they will receive contact details for future concerns and questions. Upon signing the receipt, they are compensated with 5 euros.

Any personal details collected from subjects during recruiting and experimentation will be stored encrypted for a limited time frame in a password-protected database. All data recorded during the experimentation will be anonymised and analysed separately from the personal details.

### Data analytic plan and proposed analyses

#### Pre-processing and data harvesting

First, starts and ends of utterances will be detected automatically based on the energy levels in the recorded signals. All of the starts and ends are then manually checked in the phonetic analysis software Praat [80], Together with this checking procedure, all descriptions will be manually transcribed and scored for disfluencies (restarts, corrections, hesitations, breaks) and for employed syntactic structures (e.g., transitive, intransitive, truncated passive). Based on these transcriptions, onsets and offsets of word labels are then determined with the help of the forced alignment tool provided by the Bavarian Archive for Speech Signals (BAS) [81]. The automatic annotation of speech segments is again manually checked with special attention to silent and filled pauses, as they determine the boundaries of prosodic phrases. Finally, all this information is created and stored for each sentence in the TextGrid format provided in Praat. Most importantly, the start of utterances will serve as the measure of speech onset latencies.

F0 of each sentence (in hertz) is extracted with the help of the autocorrelation method available in Praat in two passes. During the first pass, F0 tracks are extracted with default settings for the lowest and highest F0, the “floor” and “ceiling” (75 Hz and 600 Hz, respectively). Then, the first and third quartiles of F0 (Q1 and Q3) are calculated for each speaker and recorded in a table. In the second pass, F0 contours are extracted with speaker-specific settings (0.75*Q1 for floor and 1.5*Q3 for ceiling). The F0 samples making up a contour are saved in the two-column format where the first column contains timestamps and the second column F0 measures at given times.

The timing and position of eye fixations is recorded relative to the regions of depicted actors, the so-called areas of interest (AOI). The AOIs are determined on the basis of the thematic roles. This means that AOIs are defined to cover the areas of agents and patients such that the actors sharing a thematic role are enclosed into a single AOI.

For linguistic scoring, all sentences will be tagged for a number of linguistic parameters including the syntactic structure, number of actors mentioned, names of the actors, correspondence to the intended actors and mentions of any additional noun phrases or sentence modifiers. In addition, the length of sentences and syllable scores of sentence constituents and actor names are extracted from the phonetic annotations contained in the TextGrids.

A number of exclusion criteria are defined based on the eye movements, linguistic parameters, speech onset latencies and the accuracy of the verb probe task. These exclusions are necessary for the comparability between the sentences because the conceptual planning processes during language production are tightly related to speech timing and the syntactic structures employed. Therefore, target trials will be excluded when the first fixation to the AOI occurs later than 400 ms after picture onset, or when the time delay between the two consecutive fixations is longer than 600 ms (indication of track loss). Picture descriptions of a subject will be included only when (s)he is able to remember at least one word correctly in 90% of the load trials. The final analyses will only include fluent transitive sentences. After these exclusions, additional trials will be excluded based on speech onset latencies later than three standard deviations above the grand mean. Finally, all the data from the subject will be removed when the subject’s inclusion rate after the indicated exclusions is lower than 25%. No treatment of missing data is necessary because the planned regression modelling method (LMER) [82–84] is robust to unbalanced data.

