The eye movements in the existing studies are typically investigated as continuously changing functions of time in a fixed time window (from 0 to 400/600/1000 ms of picture presentation) [16–21, 69, 70]. For the purposes of this study, we derive a new relative measure from the eye movements based on what is currently known about eye movement in the linguistic task settings [16–21, 25, 69, 70]. The new metric is based on the notion of gaze that is defined as multiple consecutive fixations directed towards the region of interest [72]. As the clear start of phonological processing is indexed by a long and intense gaze towards the first-mentioned actor/object right before the onset of speech, the new measure takes this long, “naming” gaze as a landmark for the time window between the picture onset and the start of an utterance. In other words, the duration of these naming gazes will be divided by the speech onset latencies based on the following reasoning.

Namely, the time before the naming gaze indexes the time window where the conceptual frame of an incipient sentence is generated. The time after this longest gaze indicates encoding of further aspects of the incipient sentence (possibly the verb or second-mentioned actor). The highly incremental processing entails that after the picture onset, speakers start to encode the first-mentioned actors as soon as possible [18, 36, 69]. Since they might also start their speech early, they may spend most of the time period between the picture onset and the start of an utterance with processing the first-mentioned actors. In other words, the duration of the naming gaze at the first-mentioned actor relative to the speech onset latency is comparably high. Conversely, the weakly incremental planning assumes that speakers also take time for processing second-mentioned actors, such that the naming gaze at the first-mentioned actor starts later [16, 19] and the speech onset may be somewhat delayed. This means that the duration of the longest gaze towards the first-mentioned actor relative to the speech onset latency is rather low. Consequently, the degree of incrementality and the effect of cognitive load on conceptual processing can be inferred from the duration of the naming gaze measured proportionally to the speech onset latency. In particular, the increasing proportional duration of the naming gaze at the first-mentioned actor or object approximates the increase of incrementality in the conceptual planning processes.

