### Hypotheses

In line with earlier studies, active sentences uttered in response to complex visual scenes are assumed to be produced less rather than more incrementally [15, 32, 35, 65, 76]. Oppermann et al. [76] show for German that sentences with a frequent subject-verb-object ordering (e.g., ‘Die Maus frisst den Käse’, ‘The mouse is eating the cheese’) can be successfully planned in full even at the phonological planning stage. For English, Ferreira and Swets [35] similarly demonstrate that speakers plan their active sentences non-incrementally when no time constraint is imposed. Therefore, this study of Estonian assumes that the conceptual planning under low cognitive load is only weakly incremental or even non-incremental, but it is expected to become more incremental when additional cognitive load is imposed, i.e., under high cognitive load. In other words, if conceptual planning processes share resources with WM, then the detrimental effect of high cognitive load should show increase in the incrementality of conceptual planning. The effect of cognitive load on the incrementality should be observable in the increased proportional duration of the naming gaze at the actor first mentioned before the onset of speech.

As argued in the previous paragraph, sentence planning is expected to proceed weakly incrementally or even non-incrementally under low cognitive load. Accordingly, tonal variation is expected to be determined by the number of concepts maintained in the WM or by sentence length such that sentence-initial intonation peaks are higher in longer than shorter sentences. The high cognitive load and the incrementality of planning are predicted to be tightly interrelated with the advance planning of sentence intonation. First, the incrementality is expected to relate to low pitch peaks because the highly incremental conceptualization processes only foresee mentioning the first concept in subsequent utterances. Second, the cognitive load is predicted to increase the sentence-initial pitch peaks given that the mental load arising from maintaining a complex conceptual network in WM (as it may occur whilst planning long but not short sentences) is comparable to the mental load that emerges from memorizing a word list. Consequently, two different outcomes of the load manipulation on sentence-initial intonation peaks are possible (see Fig 1).

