### Materials

The materials consist of pictures showing transitive events and lists of three unrelated nouns and verbs for the verb probe task. The pictures depict three actors, two of whom share a thematic role. The two core roles of transitive events typically include i) an initiator or agent, and ii) a undergoer of the action or patient. The two thematic roles are distributed amongst the three pictured actors such that either two agents act upon a single patient (Fig 2a and 2b) or a single agent acts upon two patients (Fig 2c and 2d). This constitutes a two-level factor called Double Actor with two levels: agent and patient. A further visual factor that the design manipulates is called Identity. The two actors in the same thematic role either do or do not share their identity (e.g., they are both donkeys or they are a donkey and goat). Thus, the factor Identity includes two levels: same and different. The two visual factors with two levels are fully crossed, resulting in four pictorially controlled conditions. In particular, the four conditions show (i) same multiple agents acting on a single patient (e.g., farmers pulling a donkey), (ii) different multiple agents acting on a single patient (e.g., a male and female farmer pulling a donkey), (iii) a single agent acting on similar multiple patients (e.g., a farmer pulling donkeys), or (iv) a single agent acting on different multiple patients (e.g., a farmer pulling a donkey and goat).

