**Fig 2 pone.0259343.g002:**
[figure not shown]
An example picture in four experimental conditions eliciting short and long sentences.

The aim of this fully crossed two-factorial design is to elicit transitive sentences that differ in length, such that the similar double actor condition elicits short sentences and the different double actor condition triggers speakers to produce long sentences. The concrete task setting will ensure that the picture description will indeed be either short or long. In particular, participants are asked to describe the pictures by mentioning all three actors. Moreover, they are trained to use either plural NPs for the actors sharing the identity (e.g., ‘donkeys’) and coordinated NPs for the actors differing in the identity (e.g., ‘a donkey and a goat’).

The complex two-by-two design is necessary for the manipulation of the length effect at the two syntactic positions. This means that either the sentential subjects of prospective sentences are short or long (e.g., Mees sikutab eesleid, ‘The man is pulling the donkey’ vs Mees ja naine sikutavad eesleid, ‘The man and the woman are pulling the donkey’), or the sentential objects vary between short and long (e.g., Mees sikutab eesleid, ‘The man is pulling donkeys’ vs Mees sikutab eeslit ja kitse, ‘The man is pulling the donkey and the goat’). This design allows researchers to control for the possible interactions between the prosodic phrasing and F0 declination [4], and observe the effect of cognitive load in a worst-case scenario where the pitch peaks do not increase together with the length of object NPs.

Altogether, 64 different pictures of simple events (target items) are created for the study (4*64 = 256 pictures in total). Another set of 84 pictures will serve as distractor items. The distractor items will depict a variety of transitive and intransitive events comprising one to four identifiable actors. Half of the pictorial items are combined with a verb probe task separated into a second experimental block.

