#### Dependent variables

The dependent variables of interest are (i) speech onset latencies, (ii) duration of naming gazes, (iii) duration of naming gazes proportional to their respective speech onset latencies, (iv) the height of sentence-initial pitch peaks as indexed by F0 maxima (v) and the height of sentence-final pitch valleys as indexed by F0 minima.

First, the starts of utterances (in milliseconds) index the speech onset latencies. Second, a gaze is defined as multiple consecutive fixations directed at the AOI [72]. Gaze duration is calculated by subtracting the onset time of the first fixation directed at the AOI from the offset time of the last consecutive fixation directed to the AOI. Typically, before the speech onset, between one and five gazes occur (see Fig 5). The number of gazes usually increases together with the complexity of the visual scene. The data analysis algorithm will compare between the durations of the gazes occurring before the speech onsets and determine the gaze with the maximum duration, i.e., the longest gaze. The naming gaze is reported as missing (NA) when, in the very unlikely case of only one gaze or of two gazes of exactly the same duration, the algorithm cannot detect a gaze with the maximum duration. The longest gaze before the speech onset is called the naming gaze and submitted to further analyses together with its AOI (either agent or patient).

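### With both agents in one area of interest, adjacent looks at the second-mentioned agent raise the incrementality score where the protocol's definition says they should lower it (half of the long trials)

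*Protocol article*

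**What the plan says.** Under Pre-processing and data harvesting, AOIs follow thematic roles, and "the actors sharing a thematic role are enclosed into a single AOI". Under Dependent variables, "a gaze is defined as multiple consecutive fixations directed at the AOI"; the longest gaze before speech is the naming gaze and is "submitted to further analyses together with its AOI (either agent or patient"). Nothing in the text records which of two agents was being looked at.

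The section on the theoretical assumptions of the new measure divides the naming gaze by speech onset latency and gives the direction: "the increasing proportional duration of the naming gaze at the first-mentioned actor or object approximates the increase of incrementality in the conceptual planning processes". It also says what should lower the score: "the weakly incremental planning assumes that speakers also take time for processing second-mentioned actors", so that the gaze at the first-mentioned actor becomes a smaller share of the latency.

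Materials includes a picture condition with "different multiple agents acting on a single patient (e.g., a male and female farmer pulling a donkey"), and speakers are trained to use "coordinated NPs for the actors differing in the identity". Statistical analysis then models the proportional and the absolute naming-gaze duration on Cognitive Load x Sentence Length, pooling the two-agent and two-patient pictures within each length level.

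**The concern.** A coordinated subject (man and woman) has a first-mentioned and a second-mentioned actor, and both stand in the agent AOI. A speaker who looks from the man to the woman before speaking is recorded as making one longer gaze at the first-mentioned actor. By the protocol's own definition, that look is evidence of weaker incrementality.

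Three uses of the measure are exposed:

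- The first analysis tests whether the verb probe task made conceptual planning more incremental, and it expects a main effect of load only. The reading of the pitch results leans on that answer.
- The affected cell contains only long sentences. A scoring artefact there enters the Sentence Length effect and the Load x Length interaction on both gaze outcomes.
- The exploratory Double Actor x Identity x Load model asks whether planning increments grow with more complex scenes. A larger increment covering both agents would be scored as more incremental planning.

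**Working it through.** **Trials affected.** Design gives 64 targets per participant in 8 conditions, so 64/8 = 8 per condition. Different-identity double-agent pictures occur at two load levels: 2 x 8 = 16 of 64 (25%). Long trials number 4 x 8 = 32, so the cell is 16/32 = half of them. No short trials are affected, because same-identity agents are named by one plural noun. These are counts before exclusions and assume agent-first descriptions.

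**Direction.** Let g be the gaze on agent 1, L the latency without any look at agent 2 (g < L), and x the time on agent 2, viewed next to agent 1 and added to the latency.

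- Separate AOIs: g/(L + x), which falls as x grows.
- Merged AOI: (g + x)/(L + x). Its excess over g/L is x(L − g)/[L(L + x)], which is positive, so the score rises.

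Example with assumed times: patient 300 ms, agent 1 700 ms, agent 2 x ms, patient 200 ms, then speech, so latency is 1200 + x.

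| x (ms) | Separate | Merged |
|---|---|---|
| 0 | 700/1200 = 0.583 | 700/1200 = 0.583 |
| 200 | 700/1400 = 0.500 | 900/1400 = 0.643 |
| 400 | 700/1600 = 0.438 | 1100/1600 = 0.688 |
| 600 | 700/1800 = 0.389 | 1300/1800 = 0.722 |

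**Effect on the load contrast.** The documents give no viewing times, so the following are assumptions chosen to show a range. Low load: agent 1 500 ms, agent 2 400 ms, latency 2000 ms. This gives 500/2000 = 0.25 with separate AOIs and 900/2000 = 0.45 merged (0.25 in case D, where the looks do not merge). The other three picture cells are assumed to be scored as defined and to carry the separate-AOI effect.

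| High-load behaviour | Separate, high − low | Merged, high − low | Pooled over four cells, merged |
|---|---|---|---|
| A. Agent 2 not viewed, latency 1500 | 0.333 − 0.25 = +0.083 | 0.333 − 0.45 = −0.117 | (3 x 0.083 − 0.117)/4 = +0.033 |
| B. Both viewed as before, latency 1500 | 0.333 − 0.25 = +0.083 | 0.60 − 0.45 = +0.150 | (3 x 0.083 + 0.150)/4 = +0.100 |
| C. Agent 2 not viewed, latency 1111 | 0.45 − 0.25 = +0.200 | 0.45 − 0.45 = 0 | (3 x 0.200 + 0)/4 = +0.150 |
| D. As A, but under low load the patient is viewed between the two agents | +0.083 | +0.083 | +0.083 |

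In A the pooled load effect loses 60% (0.033 against 0.083). The long-sentence effect is (0.083 − 0.117)/2 = −0.017 against +0.083 in short sentences, so an interaction of −0.10 arises from the scoring rule alone. In C the pooled effect loses 25% (0.150 against 0.200), in B it gains 20% (0.100 against 0.083), and in D nothing changes.

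**The case against.** The strongest defence is that role-level AOIs are deliberate. The protocol ties AOIs to thematic roles, assumes that two-agent and two-patient scenes need the same early relational decision, and in places speaks of first-mentioned actors in the plural. If the whole subject is the first-mentioned unit, the measure is coherent. This does not fit the rest of the text. Materials counts three actors per picture, two of whom share a role; The present study counts a donkey and a goat as more concepts than a donkey; and Hypotheses says that "the highly incremental conceptualization processes only foresee mentioning the first concept in subsequent utterances". The assumption about similar planning concerns behaviour, not how gaze is scored.

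Several limits do stand:

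- A reader might infer that the load effect in the first analysis reverses. The documents do not support that. Reversal within the cell needs adjacent looks at both agents, a merged run that is the longest gaze, and load that removes the second look without shortening latency too far. Even in case A the pooled effect stays positive.
- A reader might infer that the pitch tests are compromised. The pitch models contain no gaze variable; only their interpretation draws on the gaze result.
- A reader might take Hypotheses as also stating that looks at the second-mentioned actor lower the proportion. Only the section on the new measure says so.
- The planned exploratory three-way model would isolate this cell, and raw eye movements will be published. Both help, but neither changes the measure used in the main analysis.
- Splitting AOIs only in different-identity pictures would be a poor remedy: AOI granularity in double-agent scenes would then vary with Sentence Length and create a new rule-driven length effect.

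**Conclusion.** The point holds as a conflict between the AOI and gaze rules and the stated meaning of the measure. It is confined to different-identity double-agent pictures described agent-first. There, adjacent looks at the second agent move the proportional score the wrong way. The likely consequences are an attenuated load effect in the first analysis and a rule-driven Sentence Length effect or Load x Length interaction in the two gaze outcomes.

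The direction of the scoring error follows algebraically once the two looks are adjacent and form the longest gaze. Its size, and whether the load effect in that cell reverses, depend on viewing patterns that the documents do not give. The other three picture cells, described agent-first, are scored as defined.

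**What to change.** 1. Prespecify the load effect on both gaze outcomes in single-agent pictures as a named confirmatory or key sensitivity result for the first analysis. There the first-mentioned actor is alone in its AOI in both length conditions.
2. Draw one AOI per depicted actor and use the same granularity in same- and different-identity double-agent pictures, so that AOI size does not vary with Sentence Length. For same-identity pairs, where one plural noun names both, state in advance which figure's gaze counts.
3. Report the merged-AOI result alongside.

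This needs re-scoring of recorded fixation positions and no new data. Smaller AOIs make some border fixations uncertain. The single-agent analysis uses 32 of 64 targets per participant; if trial-level noise dominates, its standard error is larger by up to √(64/32) = 1.41. Fixing the rules before the gaze data are analysed avoids a post hoc choice between scorings.
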